Several trials have indicated that acupuncture may alleviate the skin lesions and improve the QoL of patients with AV [11–15]. However, these trials were affected by potential bias due to small sample sizes, nonplacebo/sham/waiting list control, or use of self-defined outcome measures; thus, they did not provide robust evidence of the efficacy of acupuncture in patients with AV. Therefore, we conducted a pilot trial (unpublished) from April 2017 to March 2018 in which 42 patients with moderate or severe AV were randomly allocated to an acupuncture group (*n* = 21) or a sham acupuncture group (*n* = 21). After a 4-week treatment, the number of inflammatory lesions in the acupuncture group (*n* = 21) was 35.62 ± 15.51, with a reduction of 6.62 ± 15.42 from baseline. The number of inflammatory lesions in the sham acupuncture group (*n* = 21) was 30.05 ± 21.16, with a reduction of 15.10 ± 20.13 from the baseline. The difference between the two groups was 8.48 ± 7.74, and there was no significant between-group difference with the *p* = 0.137 due to *p* > 0.05 was considered nonsignificant. These findings contradict the results of previous trials [11–14], and authors of a systematic review of AV also reported that there was no difference between acupuncture and the waiting list for reducing the number of inflammatory lesions [16]. Unlike drugs, which act directly on the pathogen, acupuncture restores normal functions through motivating or inducing the inherent regulatory system [17]. Therefore, acupuncture may relieve other symptoms of AV (itch or pain) [18, 19] and improve the QoL [11]. The Skindex-16 scale is a sensitive and specific tool for assessing the symptoms and QoL of patients with AV, and it includes seven questions related to the symptoms (itch or pain) and characteristics (skin lesions) of AV [20, 21]. Following the 4-week treatment, the total score on the Skindex-16 scale for acupuncture (*n* = 21) was 19.89 ± 15.40, with a reduction of 12.50 ± 19.09 from the baseline. The total score on the Skindex-16 scale for sham acupuncture (*n* = 21) was 30.43 ± 19.39, with a reduction of 0.40 ± 21.12 from the baseline. The difference between the two groups was − 12.9 ± 11, and there was a significant between-group difference in this instance with the *p* = 0.044 due to *p* < 0.05 was considered statistically significant. Therefore, the results of our pilot study indicated that acupuncture may help to relieve total symptoms and improve the QoL of patients with moderate or severe AV. So far, there are two systematic reviews that recommend using the measure of QoL for evaluating the effect of acupuncture on AV [10, 16], but no clinical trials have been conducted that use the measure of QoL to evaluate the effect of acupuncture on the symptoms and the QoL of patients with AV. Therefore, we intend to use the Skindex-16 scale as a primary outcome measure in our planned study to evaluate the effect of acupuncture compared with sham acupuncture on the symptoms and QoL of patients with moderate or severe AV.

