### Randomization and allocation concealment

The randomization scheme has been prepared by the National Clinical Drug Testing Institute of the Guang’anmen Hospital. Participants will be randomly assigned to receive acupuncture or sham acupuncture treatment in a 1:1 ratio with the fixed block of 4. Sealed opaque envelopes will be used to ensure randomization concealment. The number of the randomization sequence and information on group allocation will be sealed in ordered envelopes. With the inclusion of patients, those envelopes will be opened one by one in sequence. The envelopes will be kept by a research assistant who is not involved in the treatment or assessment. Additionally, assistant researchers will perform a baseline assessment of all participants (− 1 week to 0 week) prior to randomization.

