### Outcome measures

The primary outcome will be the change in the total score of the Skindex-16 scale from baseline at the end of 4-week treatment. The Skindex-16 scale is a brief, skin-related QoL scale with satisfactory reliability and validity [20, 21]. It is used to evaluate the efficacy of acupuncture in improving the QoL of patients with AV [20, 21]. The scale includes a total of 16 items that are categorized into three domains: the symptoms of participants with AV, the emotions of participants with AV, and function of participants with AV [20, 21]. The Skindex-16 scale score ranges from 0 (best) to 100 (worst), with a minimal clinically important difference (MCID) as 10 [20, 21].

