### Sample size and statistical analysis

The sample size of this trial was calculated on the basis of primary outcome, which is the change from baseline in the Skindex-16 scale score at the end of week 4. In our unpublished pilot trial, the mean (± standard deviation) reductions in the Skindex-16 scale score after 4-week treatment in the acupuncture and sham acupuncture groups were 12.50 ± 19.09 and 0.40 ± 21.12, respectively. Assuming an alpha risk of 5% and a beta risk of 20%, a sample size of 100 (50 participants in each group) was calculated, considering a 20% dropout rate.

The data will be analyzed using IBM SPSS Statistics version 20.0 software (IBM Corp, Armonk, NY, USA) according to the intention-to-treat principle. Normally distributed continuous variables will be reported as mean ± standard deviation or 95% confidence intervals; non-normally distributed continuous variables will be reported as median (interquartile range). Categorical variables will be presented as frequency (percent). For data pertaining to dropouts, the actual observational value of the last observation will be used for statistical analysis. Between-group differences with respect to normally distributed continuous variables will be assessed using analysis of variance, and those with respect to non-normally distributed continuous variables will be assessed using nonparametric tests for the primary outcome and the secondary outcomes. Data pertaining to the participants’ expectations of acupuncture and the safety evaluation will be analyzed using the chi-square test or Fisher’s exact test. For the blinding assessment, the percentage of participants choosing traditional acupuncture will be assessed using the chi-square test. All *P* values will be two-tailed; *P* < 0.05 will be considered indicative of statistical significance.

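### The primary test and effect measure depend on whether the observed Skindex-16 changes look normal, so the primary analysis is not fixed in advance

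*Protocol article*

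**What the plan says.** All references are to the protocol article.

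- **Endpoint** (Outcome measures section): "The primary outcome will be the change in the total score of the Skindex-16 scale from baseline at the end of 4-week treatment". Scores run from 0 to 100, "with a minimal clinically important difference (MCID) as 10".
- **Test** (Sample size and statistical analysis): analysis of variance for normally distributed continuous variables; "those with respect to non-normally distributed continuous variables will be assessed using nonparametric tests for the primary outcome and the secondary outcomes". The primary outcome is named in that rule.
- **Summary** (same section): mean with SD or 95% CI if normal, median with interquartile range if not.
- **Sample size** (same section): built on pilot mean reductions, which in the "acupuncture and sham acupuncture groups were 12.50 ± 19.09 and 0.40 ± 21.12, respectively". It gives 50 per arm, allowing for 20% dropout, at 5% alpha and 80% power; P "values will be two-tailed".
- **Dropouts** (same section): the last recorded value is used.
- **Schedule** (Table 1): Skindex-16 at baseline and weeks 4, 16 and 28, with nothing at weeks 1 to 3.

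**The concern.** The article does more than leave the test open. It lays down a rule under which the observed data decide both the test and the quantity reported. One branch compares mean changes, which is what the trial is sized for. The other yields a P value and two group medians. No difference between groups in score points, and no interval for one, is attached to that second branch, so the result could not be set beside the 10-point MCID in the form planned. The Skindex-16 change could also be reported as means at one visit and medians at another, which makes weeks 4, 16 and 28 hard to compare.

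The dropout rule adds to this. A participant who leaves before week 4 has only the baseline Skindex-16 score, so the carried-forward change is exactly 0. A cluster of identical zeros is the kind of feature that a normality check picks up. Dropout could then decide which primary analysis is run.

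**Working it through.** **1. The plan's sample size is a comparison of means.** Pooled SD = √[(19.09² + 21.12²)/2] = √405.24 = 20.13. Per arm, n = 2(1.960 + 0.842)² × 405.24 / d² ≈ 6361/d².

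- d = 12.9, the Background's figure ("12.9 ± 11, and there was a significant between-group difference in this instance"): 6361/166.41 = 38.2, so 39; with the t distribution 40. Dividing by 0.8 gives 49 or 50 per arm. The stated 100 is reproduced.
- d = 12.50 − 0.40 = 12.1, from the reductions as printed: 6361/146.41 = 43.4, so 44; 44/0.8 = 55 per arm, 110 in total. The stated 100 is not reproduced.

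Which difference is right is a separate matter (the sign of the sham change). Both are carried below.

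**2. How often would the test switch?** The article gives no normality check, so one is assumed: Shapiro-Wilk at 5%, with a rank test used if either arm is rejected. There are 50 per arm. Completers are drawn from normal distributions with the pilot SDs; the acupuncture mean is 12.5 and the sham mean 0.4 (difference 12.1) or −0.4 (difference 12.9). In each arm, k values are set to 0 to represent dropout before week 4. The means test is a two-sided t-test (equal to ANOVA with two arms) and the rank test is Mann-Whitney. There are 2,000 simulated trials per scenario. Entries are percentages, for differences of 12.1 / 12.9.

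| Zeros per arm | Switch to rank test | Power, means test | Power, rank test | Power, gated rule | Tests disagree |
|---|---|---|---|---|---|
| 0 | 10.8 / 9.4 | 85.6 / 89.0 | 84.0 / 88.1 | 85.8 / 88.8 | 4.9 / 3.0 |
| 3 (6%) | 13.2 / 12.8 | 83.0 / 84.8 | 80.3 / 83.2 | 82.4 / 84.6 | 5.5 / 5.0 |
| 5 (10%) | 19.2 / 19.2 | 80.0 / 85.4 | 77.5 / 83.0 | 79.3 / 84.4 | 5.8 / 5.0 |
| 10 (20%) | 61.0 / 60.4 | 76.8 / 80.8 | 73.6 / 76.5 | 74.0 / 77.8 | 9.2 / 8.4 |

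The simulation standard error is about √(0.6 × 0.4/2000) = 1.1 points for a rate near 60%, and √(0.05 × 0.95/2000) = 0.5 points for a rate near 5%.

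**3. Cost of the gate itself** (fixed means test minus gated rule). With no zeros: 85.6 − 85.8 = −0.2 and 89.0 − 88.8 = 0.2. With 5 zeros: 0.7 and 1.0. With 10 zeros: 76.8 − 74.0 = 2.8 and 80.8 − 77.8 = 3.0. So the cost is 0 to 3 points. The larger fall down the means-test column comes from the zeros, not from the gate.

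**4. Type I error** (both means 0.4). The gated rule rejects in 4.9%, 4.8%, 4.7% and 4.6% of trials with 0, 3, 5 and 10 zeros per arm.

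**5. Dependence on the unstated check.** With 10 zeros per arm, across the scenarios including no difference, Shapiro-Wilk switches in 53–61% of trials applied in either arm, 70–72% pooled and 35–56% on residuals. A Lilliefors test switches in 95–96%, 100% and 64–95% respectively.

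**The case against.** The rule is written down beforehand and the statisticians are blinded to allocation (Blinding). Which normality check and which rank test to use are details that a condensed article may leave to the analysis plan. That is fair, and their absence is not the point. What remains is the rule itself, which the article states.

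Five stronger readings are tempting, and the documents do not support them.

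- *False positives are inflated, or the analyst may pick the better P value.* Applied mechanically, the gate keeps type I error near 5%.
- *The test would often switch.* The 20% is a planning allowance that is not tied to week 4, and follow-up runs to week 28. Only losses before week 4 produce zeros in the primary outcome. The pilot reports all 21 per arm after treatment, although imputed values there cannot be excluded. With 3 zeros per arm the switch rate is about 13%, close to the 10% with none.
- *A rank analysis cannot be read against the MCID.* A Hodges-Lehmann shift with an interval would be in score points. The accurate statement is that none is planned. The article also gives the 10 points as a property of the scale, not as a decision threshold.
- *The switch blocks baseline adjustment.* The analysis of variance branch mentions no covariate either, so nothing planned is lost.
- *The nonparametric branch has no merit.* The table assumes normal completers, which favours the means test. With strongly skewed completers (an illustrative shifted lognormal, sigma 0.8, same means and SDs, no dropout), power was 83% for the t-test and over 99% for the rank test.

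**Conclusion.** The point holds in a limited form. The article makes the primary test and its summary measure conditional on the observed distribution, while the sample size and the MCID are both on the scale of score points. This follows from the text and needs no simulation. The harm is an effect measure that is not fixed, plus some chance that the choice of test decides significance: about 3–9% of simulated trials with a true difference. It is not a loss of type I error control, and the power cost is small.

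The switch rates of about 10%, 20% and 60% rest on three assumptions that the article does not state: a formal Shapiro-Wilk test at 5% in either arm, normal completer data, and losses of 0, 10% and 20% before week 4. The 60% is an upper scenario in which all the planned dropout occurs before week 4. The change is worth making because it costs little, not because the present rule would invalidate the trial.

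**What to change.** Name one primary analysis that applies whatever the observed distribution: ANCOVA of the week-4 change in Skindex-16 total score on treatment, with baseline Skindex-16 as covariate and heteroscedasticity-robust standard errors. Report it as an adjusted mean difference with 95% CI and read it against 10 points. Keep a rank-based analysis only as a labelled sensitivity analysis. Apply the same rule to the continuous secondary outcomes analysed as change from baseline. The handling of dropouts needs its own decision; this change does not remove the zeros.

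The cost is wording. The baseline score is already collected (Table 1), the planned 100 need not change on this account, and Trial status reports no current recruitment. The one downside is that some power may be lost relative to a rank test if the change scores turn out strongly skewed.

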### Study recruitment

Participants will be recruited between August 2019 and December 2020 at the Guang’ anmen Hospital via advertisements on posters, the WeChat app, and hospital websites. A dermatologist will be responsible for the screening, which will include diagnosis of the type of acne of patients and a series of physical examinations (discrimination between inflammatory and noninflammatory lesions of AV by the pictures of participants’ faces obtained using a digital camera) according to the diagnostic criteria for AV [2, 24] and the classification of lesions of AV [25], respectively.

All participants will be asked by a research assistant to read the informed consent form that describes the trial, randomization process for treatments, and the potential benefits and risks of the trial. Participants will be informed that both acupuncture and sham acupuncture may be effective for AV, and they will be randomly assigned to the acupuncture group or the sham acupuncture group. Participants will be allowed to withdraw from the trial at any time. Written informed consent will be obtained from all subjects prior to their enrollment.

The demographic and clinical characteristics of the participants at baseline will be recorded by a research assistant: age, sex, race, body mass index (in kg/m^2^), marital status, education level (primary education or below, secondary education, and tertiary education), time of sports activity (0–3 times/month, 1–2 times/week, 3–4 times/week, and ≥ 5 times/week), daily sleep duration (< 7 h, 7–9 h, and > 9 h), smoking history, history of alcohol intake, AV duration in months, and severity of AV as assessed by Global Acne Grading System (GAGS) score (none [0 score], mild [1–18 score], moderate [19–30 score], severe [31–38 score], and markedly severe [> 39 score]) [26].

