### Blinding

The participants, outcome assessors, and statisticians will be blinded to the group allocation. However, because of the characteristics of acupuncture, acupuncturists will not be blinded in this trial. To assess the blinding effect of sham acupuncture, participants will be asked to answer the following questions within 5 min after any treatment in week 4: “Do you think you have received traditional acupuncture?” The response options will be “yes,” “no,” or “unclear.” The study protocol is illustrated in Fig. 1.

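### The only stated blinding analysis, a chi-square test on the share of *yes* answers in week 4, merges *no* with *unclear* and has too little power for a non-significant result to show that blinding held.

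*Protocol article*

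**What the plan says.** - **Question and timing.** Under Blinding, "participants will be asked to answer the following questions within 5 min after any treatment in week 4". One question follows: "Do you think you have received traditional acupuncture". Three answers are offered: *yes*, *no* and *unclear*. Table 1 marks the blinding assessment at week 4 and at no other time.
- **Analysis.** Under Sample size and statistical analysis, "For the blinding assessment, the percentage of participants choosing traditional acupuncture will be assessed using the chi-square test". All P values "will be two-tailed", with 0.05 as the threshold. No criterion for successful blinding is given.
- **Size.** "Assuming an alpha risk of 5% and a beta risk of 20%, a sample size of 100 (50 participants in each group) was calculated", allowing for 20% dropout.
- **Primary outcome.** "The primary outcome will be the change in the total score of the Skindex-16 scale from baseline at the end of 4-week treatment". Skindex-16 is a quality-of-life questionnaire, and its assessment falls in the same week as the blinding question.
- **What participants are told.** "Participants will be informed that both acupuncture and sham acupuncture may be effective for AV".

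**The concern.** The primary outcome is the participant's own rating, as are the DLQI and the itch and pain scales. The acupuncturists are not blinded. The two procedures also feel different: the Acupuncture group section describes deep insertion with manipulation to produce de-qi, and the Sham acupuncture group section describes 1–2 mm insertion with neither. A difference in Skindex-16 can be read as an effect of acupuncture only as far as participants did not know their arm. The week-4 question is the one planned check of that.

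As specified, the check has two weaknesses:

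1. **It discards information.** Three answers are collected, but the test looks only at *yes* against everything else. A sham participant who is sure of not having had traditional acupuncture counts the same as one who cannot tell. That distinction is what a blinding check in the sham arm most needs.
2. **Absence of significance says little.** A significance test asks whether the *yes* shares differ. At this sample size, moderate differences would usually go undetected.

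At stake is how much weight the report can place on a statement that blinding was maintained. The primary estimate, its test and the sample size are not affected.

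**Working it through.** The article states no figure for the blinding assessment, so there is nothing of its own to reproduce.

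**Inputs from the article.** There are 50 participants per arm and a two-sided alpha of 0.05. With 20% dropout, 50 × 0.8 = 40 per arm. Carrying the last observation forward cannot fill the gap for someone who leaves before week 4, because the question is asked only once.

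**Inputs assumed.** The share answering *yes* in each arm is not given. I take 80% in one arm and a range of 70% to 50% in the other.

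**1. Power of the stated test**

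For n per arm and *yes* shares p1 and p2, with mean p̄:

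- se0 = √[2p̄(1 − p̄)/n]
- se1 = √[p1(1 − p1)/n + p2(1 − p2)/n]
- power = Φ[(|p1 − p2| − 1.96·se0)/se1]

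Example, 80% against 65% at n = 50:

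- p̄ = 0.725
- se0 = √(2 × 0.725 × 0.275/50) = 0.0893
- se1 = √(0.16/50 + 0.2275/50) = 0.0880
- power = Φ[(0.15 − 0.1750)/0.0880] = Φ(−0.284) = 0.39

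| *Yes* shares | Power, 50 per arm | Power, 40 per arm |
|---|---|---|
| 80% vs 70% | 0.21 | 0.18 |
| 80% vs 65% | 0.39 | 0.32 |
| 80% vs 60% | 0.59 | 0.50 |
| 80% vs 50% | 0.89 | 0.82 |

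Starting from *yes* shares of 60% to 80%, the difference detectable with 80% power is about 26 to 28 points at 50 per arm and 29 to 31 points at 40 per arm.

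**2. What one non-significant result would leave open**

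Take 40/50 against 33/50 answering *yes*.

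- Pearson chi-square = 2.49, p = 0.115.
- Difference = 0.80 − 0.66 = 0.14.
- Standard error = √(0.80 × 0.20/50 + 0.66 × 0.34/50) = 0.0877.
- 95% confidence interval = 0.14 ± 1.96 × 0.0877, or −3 to +31 points.

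The test is non-significant, yet a difference of 30 points is not excluded.

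**3. What merging *no* with *unclear* hides**

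Take illustrative answers, in the order *yes*/*no*/*unclear*, of 30/4/16 in the acupuncture arm and 30/16/4 in the sham arm. The *yes* share is 60% in both, so the stated test gives chi-square 0. Four times as many sham participants have correctly said that they did not receive traditional acupuncture.

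Bang's index for an arm is BI = (correct − incorrect)/n. Its standard error is √{[pc + pi − (pc − pi)²]/n}, where pc and pi are the shares guessing correctly and incorrectly. In the sham arm, *no* is the correct answer.

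- Sham arm 30/16/4: BI = (16 − 30)/50 = −0.28, standard error √[(0.92 − 0.0784)/50] = 0.130, 95% confidence interval −0.53 to −0.03.
- Sham arm 30/4/16, for comparison: BI = (4 − 30)/50 = −0.52, standard error √[(0.68 − 0.2704)/50] = 0.091, 95% confidence interval −0.70 to −0.34.

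The index and the three-way table separate the two situations. The *yes* share cannot.

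**The case against.** **No pass/fail rule.** A reader might infer that the plan treats a non-significant chi-square as proof of blinding. The article does not say this. It names a test and gives a general significance threshold, and any rule for interpretation may sit in a fuller document. This part of the objection stands, so the point concerns what the test can show and not a rule the trial has adopted.

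**The answers are not lost.** All three are collected in each arm, and the article says that categorical variables will be shown as frequencies and percentages. This also stands: the weakness lies in the stated analysis, not in data collection. If a three-category chi-square were meant, it would detect the pattern in step 3, but the text names only the share choosing traditional acupuncture.

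**Low power is not the same as missed unblinding.** With 80% against 65% answering *yes*, most sham participants believe they had traditional acupuncture. Their Bang index is at most 0.35 − 0.65 = −0.30, which does not indicate an unblinded sham arm. This is correct. The power figures show only that non-significance is uninformative about moderate imbalance. It is a further reason to prefer an index for each arm over a comparison of *yes* shares.

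**Timing.** A reader might infer that a week-4 question is an error because guesses then mix with perceived benefit. The article offers no evidence either way. Week 4 captures belief when the primary outcome is rated. A week-1 question covers at most 3 of 12 sessions and may prompt participants to think about allocation. The timing is a trade-off. What remains is that an imbalance at week 4 has more than one explanation, and the report should say so.

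**Conclusion.** The concern holds in a limited form. The one stated blinding analysis uses part of the information collected, and its power is about 0.2 to 0.6 for differences of 10 to 20 points in the *yes* share at 50 per arm, or about 0.2 to 0.5 at 40 per arm. It becomes adequate only for differences near 30 points. These figures rest on an assumed 80% *yes* share in one arm. The limitation that non-significance cannot establish blinding does not depend on that choice.

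The documents do not support saying that the trial equates non-significance with success, that guessing in each arm goes unmeasured, or that asking in week 4 is wrong. The point is about analysis and reporting. It bears on how far a participant-rated result can be credited to acupuncture itself, and not on the primary analysis.

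**What to change.** In Sample size and statistical analysis, replace the chi-square test on the *yes* share as the blinding analysis with the following, all from the week-4 answers already planned:

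- the counts and percentages of *yes*, *no* and *unclear* by arm;
- Bang's blinding index with a 95% confidence interval, separately for each arm;
- a sentence that a non-significant P value is not evidence that blinding succeeded;
- a sentence that an imbalance may reflect perceived benefit as well as recognition of the procedure, because the question is asked in the same week as the primary outcome.

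This needs no new data, visits or participants. The cost is a few lines of text and a simple calculation, and the article reports that recruitment is not under way.

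An additional question in week 1 is optional. It would help to separate early recognition of the procedure from later perceived benefit, with the drawbacks given above, and it should not become the main check. I would not add an analysis of the primary outcome by guess: the guess is made after randomisation, so conditioning on it would not give a clean comparison.
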